### 2.13 Adverse events

Common treatment-related adverse events include acupuncture breakage, fainting during needling, local hematoma, infection, and abscess, though other discomforts can also occur after acupuncture (referring to post-acupuncture symptoms such as post-needling pain, nausea, vomiting, palpitations, dizziness, headache, anorexia, and insomnia). During the implementation of the project, specific record forms will be created, and patients will be asked whether any of the above situations have occurred during each diagnosis and treatment session. If so, these situations will be recorded immediately. Adverse event data will include the occurrence, duration, and severity of adverse reactions (symptoms and signs), as well as how the events were resolved (or unresolved) during treatment. Any adverse events occurring in subjects during the trial, including laboratory test abnormalities, will be carefully inquired about and investigated. Abnormal laboratory values or examination results are only considered adverse events when they cause clinical symptoms or signs, are considered clinically significant, or require treatment. All adverse events will be assessed in terms of their nature, severity, and correlation with medication and strictly recorded in the case report form. In the event of a serious adverse reaction, the team leader's unit and the reporting unit will be notified within 24 h, and a serious adverse event form will be filled out in this case. The handling of serious adverse events is reported, managed, and followed up on according to Good Clinical Practice principles. Handling methods may include one or more of the following: taking no action (i.e., further observation only); adjusting/temporarily suspending research treatment; permanently stopping research treatment due to the adverse event; adding concomitant drug treatment; administering non-drug treatment; admitting the patient to the hospital; or extending the patient's hospital stay. The measures taken to handle adverse events will be recorded on the adverse event page of the CRF.

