Generalized anxiety disorder (GAD) is characterized by widespread and persistent anxiety, accompanied by palpitations, sweating, tremors, dry mouth, sleep disturbances, irritability, poor concentration, and muscle tension, often starting in adolescence or early adulthood. GAD is often comorbid with other types of anxiety disorders and mood disorders, with sleep disorders or insomnia being one of the most predominant comorbidities (6). Sleep disorders are very common in individuals experiencing anxiety and are a defining criterion for many anxiety or anxiety-related disorders (7). Individuals suffering from anxiety often exhibit sleep disturbances, particularly sleep deprivation (8), that can trigger or further exacerbate anxiety symptoms (9). Psychobiological models suggest that a state of hyperarousal is a key factor in insomnia (10–12). Insomnia may be due to excessive cognitive dysfunction, maladaptive behaviors, physiological hyperarousal, and mental hyperarousal. Individuals suffering from insomnia often worry about sleep deprivation and the consequences of sleep deprivation; therefore, their anxiety-related beliefs, attitudes, and behaviors contribute to the persistence or worsening of sleep disturbances and severely shorten sleep duration (13). In summary, sleep deprivation is an important risk factor for generalized anxiety disorder and its common comorbidity, and there is an interactive relationship between the two.

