### 2.3 Inclusion criteria

The inclusion criteria are as follows:

1) Between 18 and 25 years of age.2) An average sleep duration equal to or < 6 h per night in the past 30 days.3) A score of ≥5 points on the 7-item Generalized Anxiety Disorder Scale (GAD-7).4) No anti-anxiety or insomnia-related medications taken or acupuncture treatments for anxiety or insomnia received in the most recent 30 days.5) Willingness to participate in the clinical study and sign an informed consent form.

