#### 2.12.1 Primary outcome

The primary outcome measure will be the Hamilton Anxiety Rating Scale (HAMA). Developed by psychiatrist Max Hamilton in 1959, HAMA aims to provide a quantified and standardized method for assessing anxiety symptoms (33). It was one of the first scales in the field of mental health and continues to be widely utilized. HAMA consists of 14 items, each targeting different anxiety symptoms or signs. These items include emotional anxiety, somatic anxiety, insomnia, intellectual functioning, somatic symptoms, behavioral symptoms, fear of illness, psychological symptoms, reproductive symptoms, gastrointestinal symptoms, respiratory symptoms, cardiovascular symptoms, muscle symptoms, and sensory organ symptoms. Scores for each item range from 0 (no symptoms) to 4 (severe symptoms). The total score ranges from 0 to 56 points. Higher scores indicate more severe anxiety symptoms. A score > 17 indicates mild anxiety, while scores between 25 and 30 are considered moderate to severe anxiety (34). HAMA is used not only in clinical assessments, but also in research settings to evaluate the effectiveness of drug treatments, to monitor changes in anxiety symptoms, or to serve as a diagnostic tool. HAMA is thus a comprehensive and complex tool for assessing and monitoring anxiety symptoms in adults. The reliability and validity of HAMA are adequate (Cronbach's alpha is 0.921, and validity is 0.529–0.727) (35, 36). With wide applications in both clinical and research environments, it has become one of the standard tools in the field of mental health.

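### Palpitations and insomnia are solicited as adverse events in a population likely to have them already, with no pre-treatment record, no new-or-worse rule, and relatedness judged against medication

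*Protocol article*

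**What the plan says.** Section 2.13 (Adverse events) opens with needle events, which it calls common and treatment-related: breakage, fainting, local hematoma, infection and abscess. It then adds a second group, "though other discomforts can also occur after acupuncture", explained as "referring to post-acupuncture symptoms such as post-needling pain, nausea, vomiting, palpitations, dizziness, headache, anorexia, and insomnia". That makes 5 + 8 = 13 listed items.

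The solicitation rule covers both groups: "patients will be asked whether any of the above situations have occurred during each diagnosis and treatment session". The recording rule follows directly: "If so, these situations will be recorded immediately". Occurrence, duration, severity and resolution are to be collected. The relatedness step reads: "All adverse events will be assessed in terms of their nature, severity, and correlation with medication".

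Two other places describe who is enrolled. Section 1.1 says the disorder is "accompanied by palpitations, sweating, tremors, dry mouth, sleep disturbances, irritability, poor concentration, and muscle tension". Section 2.3 requires "An average sleep duration equal to or < 6 h per night in the past 30 days".

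Section 2.17 (Data analysis) compares safety indicators between the acupuncture and sham arms.

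**The concern.** Two of the solicited symptoms are, on the article's own account, plausible features of the condition under treatment. A participant who had palpitations or slept badly before the first session can truthfully answer yes at every session. Nothing stated separates that answer from a symptom that needling caused or worsened.

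Two things are at stake. First, the absolute rates reported for palpitations and insomnia, and for any pooled any-event figure, would include pre-existing symptoms in both arms. Second, the comparison between arms for those figures would be diluted toward no difference. The relatedness step could in principle sort this out, but it is worded for a drug, and section 3 (Discussion) says the trial has no drug group.

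Timing adds to the case. If the symptom list is not completed before the first needling, that information cannot be reliably recovered later.

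**Working it through.** **No figure to reproduce.** The article gives no adverse-event rate, no background symptom rate and no power for safety. What follows is a reading of the text and then an illustration on assumed rates.

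**Overlap with the condition.** Of the 13 listed items, palpitations appear by name in section 1.1, and insomnia corresponds to the sleep disturbances named there and to the sleep criterion in section 2.3. The other six discomforts (post-needling pain, nausea, vomiting, dizziness, headache, anorexia) and the five needle events are not in that description. So 2 of 13 items are tied to the condition.

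**Threshold for counting.** Section 2.13 does set a threshold for laboratory values: they count only if they cause symptoms, are clinically significant or need treatment. It sets none for symptoms.

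**Size of the dilution.** Inputs: b = share of participants in each arm recorded because of a symptom already present (assumed); e = incidence caused by needling, acupuncture arm only, independent of b (assumed); n = 28 per arm (section 2.15); two-sided α = 0.05 (section 2.17).

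- Recorded rate, acupuncture: b + (1−b)e. Recorded rate, sham: b.
- Recorded difference: (1−b)e.
- Share of recorded acupuncture cases already present: b / [b + (1−b)e].

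For e = 20%, with power from the normal approximation for two proportions:

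| b | acupuncture vs sham | difference | share already present | power |
|---|---|---|---|---|
| near 0 | about 20% vs 0% | 20 points | near 0 | about 0.71 |
| 10% | 28% vs 10% | 18 points | 36% | 0.40 |
| 30% | 44% vs 30% | 14 points | 68% | 0.19 |
| 50% | 60% vs 50% | 10 points | 83% | 0.11 |
| 70% | 76% vs 70% | 6 points | 92% | 0.07 |

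The approximation is rough near zero. With Fisher's exact test (summing binomial probabilities over all outcomes with p < 0.05, 28 per arm), the first row falls to about 0.50 and the b = 30% row to about 0.13. The pattern is the same. For e = 10%, the share already present runs from 53% at b = 10% to 96% at b = 70%.

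**When pre-existing symptoms are the majority.** b > (1−b)e gives b > e/(1+e): 0.20/1.20 = 16.7% for e = 20%, and 0.10/1.10 = 9.1% for e = 10%.

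**If the background does not stay equal.** Section 3 expects two weeks of treatment to improve sleep-deprivation symptoms. Suppose (assumed) the background is 40% with acupuncture and 60% with sham, and true new events are 15% and 5%. Recorded rates are 0.40 + 0.60 × 0.15 = 49% and 0.60 + 0.40 × 0.05 = 62%. The arm with more true events would show the lower rate. This is a possibility, not a prediction.

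**The case against.** The strongest reply is that this is a condensed article. It says specific record forms will be created and refers to an adverse-event page of the case report form; neither is shown, and a baseline symptom check could sit there. That is fair, and it keeps the point to what the text states. But the text does state a rule, which is to record any positive answer, and it gives a counting threshold for laboratory values only. The medication wording is an error on the page whatever the forms contain.

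A reader might infer that pre-existing insomnia will be classed as treatment-related. The text does not support that. The label attaches to the needle events, the symptoms are introduced separately as discomforts after acupuncture, and a relatedness assessment is planned. The question can also be read as covering only what happens within a session, which would catch little long-standing insomnia; the wording allows both readings.

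A reader might also infer that adverse-event rates will mostly count existing illness, or that real harm will be hidden. The first depends on a background rate the article does not give. Short sleep is not the same as insomnia, and section 3 describes the sample as nonclinical. The second does not hold for hematoma, infection, abscess, fainting, breakage and post-needling pain, provided they are tabulated separately. The sham arm shares the background at entry, so the comparison is diluted but not void.

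There is some baseline information. The primary scale, taken at baseline, has an insomnia item and covers "gastrointestinal symptoms, respiratory symptoms, cardiovascular symptoms". It is a different instrument, palpitations are not a separate item, and nothing links it to adverse-event classification. Severity and duration records help in part.

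Finally, power for safety is low in any case: 15% vs 5% with no background at all has power of about 0.24 (normal approximation) or 0.08 (Fisher's exact test) at 28 per arm. The fix would not cure that. It would make the reported rates mean what they say.

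**Conclusion.** The point holds in a limited form. Followed as written, section 2.13 lets symptoms present before treatment into the recorded rates for palpitations and insomnia, and into any pooled any-event rate. For those figures a true excess e is reduced by the factor (1−b), under the assumptions that b is equal in the two arms and independent of needling effects. The direction is certain whenever b is above zero; the size cannot be fixed from the article. Section 2.17 does not say that a pooled rate will be used, so the effect on such a rate is conditional.

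The reference to medication in the relatedness step is a separate, plain defect: as worded, it does not ask whether the needling procedure caused the event. Both matters should be corrected before the first participant is needled. They concern the safety reporting only and leave the efficacy analysis untouched.

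**What to change.** 1. Complete the same symptom form, with severity, once for each randomised participant before the first needling.
2. State that a listed symptom counts as an adverse event only if it is absent from that record or more severe than recorded there.
3. Base the between-arm safety comparison on these new or worsened events, and tabulate local needling events (breakage, fainting, hematoma, infection, abscess, post-needling pain) separately.
4. Replace medication with the study needling procedure, real or sham, in the relatedness assessment.

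If the forms not shown already contain a pre-treatment check, one sentence in section 2.13 saying so would cover item 1. The cost is one extra use of an existing form, a few minutes per participant at baseline, and short wording changes. No treatment or visit changes.

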### 2.14 Follow-up

Follow-up will take place 2 weeks after completion of the treatment program. This time point was selected to assess the sustained long-term effectiveness of the intervention.

### 2.15 Sample size

According to the results of a pilot study (58), after 8 weeks of treatment, the HAMA scores were 9.00 ± 3.2 in the treatment group and 10.83 ± 3.06 in the control group. Sample size estimation using a two-tailed test for a study with a paired design for two-sample mean comparison, a significance level of α = 0.05 (two-tailed), and a power of 1–β = 0.90 was performed. Using PASS 15.0 to estimate the difference between the two groups' HAMA as 0.915, assuming a common standard deviation of 1.83, the sample size was estimated using a two-sample test assuming equal variances in PASS 15.0. The estimation formula (60) is:

$$\begin{array}{l} n=\frac{2\times {\left(u_{\alpha }\;+\;u_{\beta }\right)}^{2}\sigma^{2}}{\delta } \end{array}$$

Considering ~20% potential dropout during the observation period, the calculated sample size was calculated to be ~28 cases per group, and the total number of participants was determined to be 56.

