**Methods/design:**

In this randomized clinical trial, a total of 56 participants diagnosed with GAD comorbid with naturally occurring PSD and 28 healthy controls (HCs) will be recruited. The participants diagnosed with GAD comorbid with PSD will be randomly assigned to either the acupuncture group or the sham acupuncture group at a 1:1 ratio. The primary outcome measure is the Hamilton Anxiety Rating Scale (HAMA). Secondary outcome measures are the Sleep Deprivation Index (SDI), the Self-Assessment Scale for Anxiety (SAS), the Epworth Sleepiness Scale (ESS), and the State-Trait Anxiety Inventory (STAI). Additionally, three psychological paradigms (the attentional network test, psychomotor vigilance test, and emotional face Go/No-go) and event-related potential (ERP) data. Healthy volunteers will not undergo acupuncture but will instead participate in baseline assessments for the scales, mental paradigms, and ERP data. Acupuncture and sham acupuncture interventions will be conducted for 30 min, three times a week, over a 2-week period. Evaluations will be performed at zero weeks (baseline), 1 week, and 2 weeks, with the data enumerator, outcome assessor, and participant blinded to the treatment assignment.

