## 2 Methods/design

### 2.1 Study setting

This study will be a parallel randomized controlled clinical trial with the participants blinded to their groups. The research will be conducted in accordance with the principles outlined in the Consolidated Standards of Reporting Trials (CONSORT) and the Standards for Reporting Interventions in Clinical Trials of Acupuncture (STRICTA). A total of 56 participants diagnosed with GAD comorbid with naturally occurring PSD (i.e., nighttime sleep duration ≤ 6 h) will be recruited, and 28 healthy volunteers will also be recruited as a control group. Participants will be randomly assigned at a 1:1 ratio to either the acupuncture group or the sham acupuncture group. The establishment of the sham acupuncture group is intended to provide clearer evidence of the therapeutic effects of acupuncture and to compare these effects with the placebo effect of sham acupuncture. Both the acupuncture and sham acupuncture interventions will be conducted over a 2-week period, with sessions conducted three times a week. The study will be conducted at the Third Affiliated Hospital of Henan University of Chinese Medicine in Henan Province, China. The research will follow the Standard Protocol Items: Recommendations for Interventional Trials (SPIRIT) guidelines (32). For the participant timeline, see Figure 1.

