The inclusion of a healthy participant group in the trial is primarily used to explore the difference in cognitive function between subjects with comorbid GAD and PSD and normal individuals. Subjects and normal individuals will be screened through the Generalized Anxiety Disorder Scale and partial sleep deprivation index, and cognitive functions will be compared by recording EEG data to explore their intrinsic mechanisms. This trial does not set up a drug group and will analyze the indicators 1W and 2W after acupuncture by collecting data on the subjects' brain attention, cognition, and attention bias and conduct a superiority analysis with the sham acupuncture group to explore the clinical effect of acupuncture on improving GAD comorbid with PSD.

This study introduces the concept of naturalistic research to this subject area and observes individuals with comorbid GAD and naturally occurring PSD in a nonclinical sample. The objective is to investigate the biologically close relationship between naturally occurring PSD and the subsequent emergence of anxiety symptoms, as along with the underlying neurocognitive mechanisms in the brain. Applying the principles of naturalistic research to observing the relationship between naturally occurring PSD and negative emotions more closely approximates reality and yields results closer to real-life situations than designing and conducting PSD trials. In clinical observations, we have found that a 2-week intervention can improve the symptoms of sleep deprivation in patients. Choosing a 2-week treatment duration is conducive to further investigating the response time of acupuncture as an early intervention. Considering the long treatment period for GAD, acupuncture, as a low-side-effect treatment method, can aid patients in receiving long-term treatment. When combined with medication therapy, it can enhance treatment effectiveness, making it a recommended alternative therapy. This study focuses on the impact of early adulthood sleep deprivation on generalized anxiety, offering a new perspective for the prevention and treatment of GAD.

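### The planned HAMA difference rests on an 8-week pilot result with no basis given for a 2-week trial, and 28 per arm does not give the stated 90% power

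*Protocol article*

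**What the plan says.** Section 2.15 (Sample size) cites one source for the HAMA effect, a pilot study: "after 8 weeks of treatment, the HAMA scores were 9.00 ± 3.2 in the treatment group" and "10.83 ± 3.06 in the control group". It then uses PASS to "estimate the difference between the two groups' HAMA as 0.915", "assuming a common standard deviation of 1.83", with two-sided α of 0.05 and power of 0.90. The test is called a paired design in one sentence and a two-sample test with equal variances in the next. After about 20% dropout the result is given as 28 per group, 56 in total.

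The trial itself is shorter. Section 2.1 says: "Both the acupuncture and sham acupuncture interventions will be conducted over a 2-week period", three sessions a week. The abstract says: "Evaluations will be performed at zero weeks (baseline), 1 week, and 2 weeks". Section 2.14 adds a follow-up 2 weeks after treatment ends, about week 4. Section 2.12.1 names HAMA as primary outcome without a time point.

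On the choice of 2 weeks, the Discussion says "we have found that a 2-week intervention can improve the symptoms of sleep deprivation in patients", and that this length helps to study how soon acupuncture acts. Section 1.3 cites a study for a rapid reduction of anxiety with acupuncture. None of these statements gives a HAMA difference from sham at week 2.

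**The concern.** A power statement is only as good as the difference it assumes at the time of the comparison. Here the difference was observed after a course four times as long (8 weeks against 2), and the article does not say why it, or half of it, should be seen by week 2. The one stated observation about a 2-week course concerns sleep-deprivation symptoms, not HAMA, and not a contrast with sham.

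The stakes are practical. Readers are told that the HAMA comparison has 90% power. If the true figure is much lower, a non-significant result says little about whether acupuncture works, yet it would appear to come from a well-powered trial. Section 2.12 also treats the secondary results as of reference value when HAMA is significant, so low power on HAMA affects how they are read too.

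**Working it through.** **Inputs** (all from section 2.15 unless noted)
- Pilot means at 8 weeks: 9.00 and 10.83; difference 10.83 − 9.00 = 1.83.
- Pilot SDs 3.2 and 3.06; pooled SD = √((3.2² + 3.06²)/2) = 3.13 (equal arm sizes assumed); standardised difference 1.83/3.13 = 0.58.
- Planning values entered: difference 0.915 = 1.83/2; SD 1.83. The SD equals the pilot mean difference and matches neither pilot SD.
- Two-sided α 0.05, power 0.90, dropout 20%, allocation 1:1 (section 2.1).
- Evaluable per arm: 28 × 0.8 = 22.4, taken as 22.

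**Reproducing the stated 28 per group**

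For two means, n per arm = 2(1.960 + 1.282)² σ²/δ², where (1.960 + 1.282)² = 10.51.
- Printed values: 2 × 10.51 × (1.83/0.915)² = 84.1, so 85 per arm; 85/0.8 gives 107 with dropout.
- Formula as printed, with δ not squared: 2 × 10.51 × 1.83²/0.915 = 76.9, so 77 per arm.
- Pilot's own values: 2 × 10.51 × (3.13/1.83)² = 61.5, so 62 per arm; 62/0.8 gives 78.

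None of these gives 28. Two other routes come close:
- A paired t-test at 0.915/1.83 = 0.5 needs 44 pairs, and 44/0.8 = 55, close to the total of 56. This does not fit two parallel arms.
- Setting both difference and SD to 1.83 needs 22 per arm, and 22/0.8 = 27.5, so 28. This contradicts the stated 0.915, and the SD contradicts the pilot's 3.2 and 3.06.

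**Power for the planned size** (two-sample t-test, two-sided 0.05, noncentral t)

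| Difference | SD | Basis | 28 per arm | 22 per arm |
|---|---|---|---|---|
| 0.915 | 1.83 | printed planning values | 0.45 | 0.37 |
| 1.83 | 3.13 | pilot, 100% of effect by week 2 | 0.57 | 0.47 |
| 1.37 | 3.13 | 75% by week 2 (assumed) | 0.36 | 0.30 |
| 0.915 | 3.13 | 50% by week 2 (assumed) | 0.19 | 0.16 |
| 0.46 | 3.13 | 25% by week 2 (assumed) | 0.08 | 0.08 |

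**Separating the two causes**

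In the 100% row the shorter course does no harm, and power is still 0.57 (0.47). The fall from 0.90 to that level therefore comes from the difference and SD used in the calculation. Only the further fall, in the last three rows, can be put down to 8 weeks against 2, and its size depends on shares that the article does not supply.

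With SD 3.13, 90% power would need a week-2 difference of 2.76 points with 28 per arm, or 3.13 points with 22. These are 151% and 171% of what the pilot showed after 8 weeks.

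**The case against.** **A stronger reading a reader might infer:** that the sample size is set for an endpoint the trial never measures. The article does not support this. HAMA is the primary outcome and is measured. Section 2.15 cites 8-week scores as source data and does not define the endpoint at 8 weeks. Borrowing an effect from a longer course is an unsupported assumption about its size, not a conflict between two endpoints. Nor does the calculation enter the 8-week difference itself; it enters 0.915.

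**The halving might be an allowance for the shorter course.** The article does not say so. If it was, power is 0.19 (0.16) at the pilot SD and 0.45 (0.37) at the printed SD.

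**The assumed shares are guesses.** This stands. An early separation that later narrows would give a share above 100%, and the pilot's time course is not available here. The rows below 100% show sensitivity only; the shortfall from 90% does not depend on them.

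**The article gives some support for a short course.** Section 1.3 speaks of rapid anxiety reduction, and the Discussion presents 2 weeks as a way to study response time. These are reasons to study 2 weeks, but they supply no HAMA difference there.

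**The analysis may be more efficient than a t-test.** Section 2.17 lists t-tests but also a covariate-adjusted GEE for HAMA. If baseline HAMA were a covariate with correlation 0.5 to 0.7 (assumed), the SD shrinks by √(1 − r²), and power at 1.83 rises to about 0.70 to 0.85 with 28 per arm, or 0.59 to 0.76 with 22. This softens the figures but does not reach 90%, and section 2.15 does not claim such a gain.

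**Conclusion.** The point holds in two parts. First, the HAMA difference is anchored to an 8-week result, halved without explanation, and no basis is given for the value expected in a trial that treats for 2 weeks. Second, the stated 90% power is not obtained from the printed planning values (0.45 with 28 per arm, 0.37 with 22) or from the pilot's own values (0.57 and 0.47). The one combination that reproduces 28 per arm contradicts the stated difference and the pilot SDs.

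A reader might blame the whole gap on treatment length. That is not supported: the gap down to 0.57 (0.47) arises from the inputs. The duration mismatch may take power lower, to between 0.36 (0.30) and 0.08 (0.08) for assumed shares of 75% to 25%.

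These figures assume an unadjusted two-sample t-test at a single time point, equal pilot arm sizes for the pooled SD, and 20% dropout leaving 22 per arm. The 90% is wrong as written and should be corrected.

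**What to change.** In section 2.15:
1. Say that the pilot difference of 1.83 is an 8-week value.
2. Name the HAMA time point to which the calculation refers.
3. State the difference and SD assumed at that time point, with their basis. If 0.915 is kept, explain the halving; if SD 1.83 is kept, explain why it departs from 3.2 and 3.06.
4. Describe one test, the two-sample comparison that matches the parallel design, and square δ in the formula.
5. Replace 90% with the power that 28 per arm (22 evaluable) gives, as a range over the assumed share of the 8-week effect, for example 25% to 100%. If a gain from baseline adjustment is claimed, state the assumed correlation.
6. State that a non-significant HAMA result will be reported by its confidence interval and not as absence of effect.

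The 56 participants and all visits stay as planned. The cost is a text change and a less favourable power statement.

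### The HAMA sample-size inputs do not give 28 per group: they need 86 before dropout, and power with 28 randomised per arm is about 37–45%, not 90%

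*Protocol article*

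**What the plan says.** Section 2.15 of the protocol article starts from a pilot study: "after 8 weeks of treatment, the HAMA scores were 9.00 ± 3.2 in the treatment group and 10.83 ± 3.06 in the control group". It sets a two-sided 5% significance level and "a power of 1–β = 0.90 was performed". It describes "a study with a paired design for two-sample mean comparison", then says that PASS 15.0 was run for a two-sample test with equal variances. The inputs given are the difference in "HAMA as 0.915, assuming a common standard deviation of 1.83". The printed formula has 2 × (u_α + u_β)² × σ² over δ, with δ not squared. After an allowance of about 20% for dropout, "the calculated sample size was calculated to be ~28 cases per group", 56 in total.

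Section 2.1 makes the two arms parallel and independent (1:1 randomisation, acupuncture against sham), with two weeks of treatment. Section 2.12.1 makes HAMA the only primary outcome.

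**The concern.** The numbers in this one section do not fit together. The value given as the SD is far below both pilot SDs but equals the difference between the pilot means exactly, and the value given as the difference is exactly half of that. The design is called paired although the arms contain different people. The pilot result was reached after eight weeks, four times the treatment period here.

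The stated 90% power tells a reader how to weigh a non-significant result. If the true power is below one half at the planned effect, such a result says little about whether acupuncture differs from sham, yet it would carry the authority of a trial described as well powered. Section 2.12 adds to the stakes: it ties the value of the secondary results to significance on HAMA. The Discussion also promises a superiority comparison with sham.

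**Working it through.** **Inputs, all from section 2.15 unless noted.** Pilot means 9.00 and 10.83; pilot SDs 3.2 and 3.06; planned difference 0.915; planned SD 1.83; two-sided alpha 0.05; power 0.90; dropout 20%; 28 per group; 1:1 allocation (section 2.1).

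**Where 0.915 and 1.83 appear to come from.**
- Pilot difference: 10.83 − 9.00 = 1.83.
- Half of it: 1.83 / 2 = 0.915.
- Pooled pilot SD, taking equal arms: √((3.2² + 3.06²)/2) = 3.13.
- Standardised effect from the plan's inputs: 0.915 / 1.83 = 0.50. From the pilot: 1.83 / 3.13 = 0.585.

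**Attempt to reproduce 28 per group.** (u_α + u_β)² = (1.960 + 1.2816)² = 10.507.

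| Route | Needed for 90% power | After /0.8 |
|---|---|---|
| Printed formula, δ unsquared: 2 × 10.507 × 1.83² / 0.915 | 76.9 per group | 96.1 |
| Same with δ²: 2 × 10.507 / 0.5² | 84.1, so 85 per group | 107 |
| Exact two-sample t, effect 0.5 | 86 per group | 108 |
| Exact two-sample t, pilot values, effect 0.585 | 63 per group | 79 |
| Paired t, effect 0.5 | 44 pairs | 55 |
| Difference = SD = 1.83, effect 1.0, normal approximation: 2 × 10.507 = 21.0 | 22 per group | 27.5, so 28 |

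Only the last two rows come near the stated size. The paired row gives about 56 in total if 44 pairs are read as 44 people (44/0.8 = 55), which is not valid for two independent arms. The last row needs a standardised effect of 1.0, which neither the plan's inputs nor the pilot supports.

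**Power the trial has.** Unadjusted two-sample t-test, two-sided 5%, exact noncentral t. Evaluable per arm after dropout: 28 × 0.8 = 22.4, so 22.

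| Assumed difference / SD | 28 per arm | 22 per arm |
|---|---|---|
| 0.915 / 1.83 (plan) | 45% | 37% |
| 1.83 / 3.13 (pilot) | 57% | 47% |
| 0.915 / 3.13 (plan's difference, pilot SD) | 19% | 16% |

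**Effect that 22 per arm can detect.** 90% power needs a standardised effect of 1.00, which is 1.00 × 3.13 = 3.1 HAMA points. 80% power needs 0.86, or 2.7 points.

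**The case against.** The strongest defence is that section 2.17 does not rely on an unadjusted t-test alone. It plans a GEE on HAMA over time with covariates, and adjustment raises power. The protocol gives no correlation, so a range must be assumed. With the plan's effect of 0.5, a correlation of 0.5 between covariates and outcome gives about 46% power (22 per arm) to 56% (28 per arm); a correlation of 0.7 gives 62% to 73%. With 22 per arm, 90% needs a correlation of about 0.87, or about 0.81 at the pilot effect. Section 2.15 claims no such gain, and section 2.17 does not name baseline HAMA as a covariate. What stands is that the power figures must be labelled as unadjusted.

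Three further points are fair:
- The section does not say where 1.83 and 0.915 come from. That the mean difference was entered as the SD is inferred from an exact match. The shortfall does not depend on that inference, because the stated ratio of 0.5 alone produces it.
- The unsquared δ may be a typesetting slip. Correcting it raises the requirement from 77 to 85, so it does not rescue 28.
- How far an eight-week effect carries over to two weeks cannot be judged from the protocol. It is a caution about the pilot effect, not part of the arithmetic.

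**Conclusion.** The concern holds. No valid reading of section 2.15 gives 28 per group at 90% power. The stated inputs require 86 evaluable per group (108 with dropout), and the pilot values used properly require 63 (79 with dropout). Unadjusted power is 37–45% on the plan's own inputs and 47–57% on the pilot's. At the planned effect, the trial would therefore miss it more often than detect it.

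These figures assume that the ± values are SDs, that the pilot arms were of similar size (for the pooled SD of 3.13), and that the analysis is an unadjusted two-sample t-test. Covariate adjustment would narrow the gap but not close it under ordinary correlations. Because this concerns the sole primary outcome, the section must be corrected.

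**What to change.** Keep 56 participants and rewrite section 2.15:
- Remove the paired description and state a two-sample comparison of independent arms.
- Square δ in the formula and write the normal quantile for alpha/2, to match the two-sided test.
- Replace 0.915 and 1.83 with the pilot difference of 1.83 and the pooled SD of 3.13.
- State that, by an unadjusted two-sample t-test, 44 evaluable participants (22 per arm) give about 47% power for the pilot difference and 90% power only for a difference of about 3.1 HAMA points.
- Say that the pilot effect was seen at eight weeks and may not apply at two.
- Describe the efficacy comparison, including the superiority wording in the Discussion, as preliminary, and report it as an estimate with a confidence interval.

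The cost is new wording and a less favourable power statement, with no extra participants. The registry entry should be changed as well if it repeats the calculation; it was not available to check. If the sponsor prefers to keep 90% power for the pilot difference, the price is 79 per group (63/0.8), 158 in total.
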